#### Known potential benefits

Screening procedures may identify undiagnosed health problems allowing for referral to an appropriate healthcare facility based on good medical practice in The Gambia. Unrelated conditions diagnosed during trial enrolment will be referred in the same way. At the end of their participation in the trial, all toddler and infant participants will be offered an additional SC dose of a MRV with the aim of ensuring no participant remains unprotected from either measles or rubella at the end of the trial. Such administration will be undertaken outside the trial protocol. Adults are likely to benefit from additional vaccine-induced protection against measles and rubella, as they would not otherwise be eligible for the vaccine. The MRV-MNP has the potential to have a profound impact on efforts to achieve measles and rubella elimination. Measles is a serious illness which continues to be associated with high rates of mortality in sub-Saharan Africa while CRS results in both pregnancy loss and birth defects causing significant long-term disability. Participants may therefore benefit in the knowledge that they have played their part in reducing the incidence of, and ultimately eliminating these conditions in the future.

### Objectives {7}

#### Primary — safety and tolerability

To assess the safety and tolerability of a single dose of a measles and rubella vaccine administered by a microneedle patch (MRV-MNP) compared to a single dose of a measles and rubella vaccine administered subcutaneously (MRV-SC) in healthy adults (18-40 years), measles and rubella vaccine (MRV)-primed toddlers (15–18 months) and MRV-naïve infants (9–10 months) in The Gambia through to 180 days following study product administration.

#### Secondary — immunogenicity

To evaluate the immunogenicity of a single dose of MRV-MNP compared to a single dose MRV-SC in healthy adults (18–40 years), MRV-primed toddlers (15–18 months) and MRV-naïve infants (9–10 months) in The Gambia through to 180 days following study product administration

#### Exploratory objectives

To enumerate and characterize the measles and rubella-specific T-cell responses generated by MRV-MNP and MRV-SCTo describe the experience of participants and parents following study product administration by MNP compared to SC injectionTo describe the views of trial personnel regarding study product administration by MNP and to SC injection

Exploratory objectives will be assessed in a subset of participants and will not be reported as part of the primary trial analysis.

### Trial design {8}

This is a phase 1/2, single-centre, double-blind, double-dummy, randomized, active-controlled, age de-escalation trial.

All participants will receive either the MRV-MNP and a placebo (0.9% sodium chloride) SC injection (PLA-SC) or a placebo-microneedle patch (PLA-MNP) and MRV by the SC route (MRV-SC). Only those study staff randomizing participants and preparing the study products for administration will be aware of the group to which a participant belongs. Those administering the study products, all other trial staff collecting safety and immunogenicity endpoints, and the participants and parents will be blind.

Decision regarding age de-escalation will be based on a review of the safety data from the preceding cohort (adults for toddlers and toddlers for infants) up to day 14 post-study product administration by an independent data monitoring committee (DMC).

In all, 45 adults (18 to 40 years of age) will be randomized in a 2:1 ratio. Thus, 30 adults will receive MRV-MNP and PLA-SC and 15 adults will receive MRV-SC and PLA-MNP. A total of 120 toddlers (15 to 18 months of age) will be randomized in a 1:1 ratio. Thus, 60 toddlers will receive MRV-MNP and PLA-SC while the same number of toddlers will receive MRV-SC and PLA-MNP. A total of 120 infants (9 to 10 months) will also be randomized in a 1:1 ratio. Thus, 60 infants will receive MRV-MNP and PLA-SC while the same number of infants will receive MRV-SC and PLA-MNP.

Solicited local and systemic adverse events (AEs) will be collected daily from all participants from the day of study product administration to day 13 post-study product administration. Unsolicited AE and serious adverse events (SAEs) will be collected from the day of study product administration to day 180 post-study product administration. All participants will have laboratory investigations (human immunodeficiency virus [HIV], hepatitis B, hepatitis C, haematology and biochemistry) conducted as part of screening. Adults will have safety laboratory investigations repeated on day 7 and day 14 post-study product administration. Toddlers and infants will have safety laboratory investigations repeated on day 7 post-study product administration only. All cohorts could have further laboratory investigations undertaken as clinically indicated.

All participants will have measles and rubella-specific serum neutralizing antibody (SNA) titres and measles and rubella-specific immunoglobulin G (IgG) concentrations measured at baseline and on day 42 and day 180 post-study product administration.

Statistical analysis will be descriptive and aims to generate the safety and immunogenicity data required for future go/no-go decisions related to future MRV-MNP development.

## Methods: participants, interventions and outcomes

### Study setting {9}

The study will be conducted by MRC Unit The Gambia at the London School of Hygiene and Tropical Medicine (MRCG), with recruitment and all participant-related trial procedures being undertaken within specifically designed clinical trial facilities within a government hospital (Bundung Maternal and Child Health Hospital) in the West Coast region of The Gambia, West Africa. The clinical trial facilities are a short drive from the main laboratory, vaccine storage, biobanking, data management and administrative facilities of MRCG. The MRCG clinical services department (CSD), where any inpatient medical care required by study participants would usually take place is also on the same site and thus is readily accessible.

### Eligibility criteria {10}

Participants must meet all the inclusion criteria and none of the exclusion criteria to be eligible to participate. No screening procedures will take place before an individual has provided written informed consent to join the trial.

#### Inclusion criteria

A prospective participant must meet all the following inclusion criteria to be eligible for enrolment (randomization and vaccination):

Participants must:Provide voluntary written/thumb-printed informed consent for trial participation (adult cohort)Have voluntary written/thumb-printed informed consent provided for them by a parent (toddler and infant cohort)Be between 18 and 40 years inclusive on the day of consent. They will be eligible from the day they reach 18 years of age until the day before they reach 41 years of age (adult cohort)Be between 15 and 18 months of age inclusive on the day of consent. They will be eligible from the day they reach 15 months of age until the day before they reach 19 months of age (toddler cohort)Be between 9 and 10 months of age inclusive on the day of consent. They will be eligible from the day they reach 9 months of age until the day before they reach 11 months of age (infant cohort)The identity and age of all prospective participants must be as confirmed from a suitable source document prior to informed consent. Suitable source documents include but are not limited to the birth certificate, national identification card, passport and, in toddlers and infants, the parent-held infant welfare card (IWC). Photographic identification is not consistently available and is not required. Participants/parents will be issued with a trial photographic identification card once randomization and vaccination have taken place (visit 1).Be judged to be able to comprehend and comply with study requirements and procedures and must be willing and able to return for all scheduled follow-up visits (adult cohort)Have a parent who is judged to be able to comprehend and comply with study requirement and procedures and is willing and able to return for all scheduled follow-up visits (toddler and infant cohort)Be willing to avoid consumption (ingestion and topical application) of herbal or other local traditional medications throughout the course of the study. Also, be willing to avoid the use of medications (for example those available for purchase at local pharmacies) except those provided by the trial team (unless in an emergency) (adult cohort)Have a parent who is willing to ensure they avoid consumption (ingestion and topical application) of herbal or other local traditional medications throughout the course of the study. Also, who is willing to ensure they avoid the use of medications (for example those available for purchase at local pharmacies) except those provided by the trial team (unless in an emergency) (toddler and infant cohort)Have a readily identifiable place of residence within a reasonable travelling distance of the clinical trial siteThis aims to ensure home visits for solicited AE can be undertaken reliably and that the participant is able to present to the trial site or be reviewed at their home in the event of other unsolicited health complaints. No specific geographical limits are set with this regard. Rather, such decisions will be made based on the judgement of senior members of the field team based on their detailed knowledge of local geography and transport links.Have a consistent means of telephone contact for the duration of trial participation (adult cohort)Have a parent with a consistent means of telephone contact for the duration of trial participation (toddler and infant cohort)A telephone on a closed user group (CUG) network with the field team will be provided to participants/parents to ensure they are able to contact the investigator team at any time day or night without the need for telephone credit.Have a site on one wrist that is judged to be suitable for MNP administrationAdult female cohort only: have a negative serum pregnancy test at screening (visit 0) and negative urine pregnancy test on the day of vaccination (visit 1)Adult female cohort only: employ an effective method of birth control for 2 months preceding and throughout the studyEffective methods of birth control are defined as follows: credible history of continuous abstinence from heterosexual activity as a normal lifestyle choice, hormonal contraceptives (oral, injectable, implant, patch and ring), barrier contraceptives (condom or diaphragm, with spermicide) and intrauterine device. When using contraceptives, participants must have been using their current contraceptive for the past 2 months to be eligible. Adult female participants with documented sterilization via tubal ligation or hysterectomy may be enrolled although for completeness all female participants will undergo pregnancy testing as outlined above. Participants will never be encouraged to start using contraception to allow them to be eligible to join the study.Toddler cohort only: have been parenterally vaccinated against measles and rubella at between 9 and 12 months of ageBe willing to avoid MRV administration for the duration of enrolment in the study, including in the case of a national MRV campaign in The Gambia (adult cohort)Have a parent who is willing to ensure they avoid MRV administration for the duration of enrolment in the study, including in the case of a national MRV campaign in The Gambia (toddler and infant cohort)All toddlers and infants in the study will receive an additional SC dose of an MRV so will not miss out. Adults are not routinely included in MRV campaigns but will be given any missed doses under these circumstances.Be willing to avoid all vaccines not given by the trial team for the duration of the study except for non-measles and rubella vaccines given in national campaignsHave a parent who is willing to ensure they avoid all vaccines not given by the trial team for the duration of the study except for non-measles and rubella vaccines given in national campaigns (toddler and infant cohort).

#### Exclusion criteria

A prospective participant will not be eligible for enrolment if they meet any of the following exclusion criteria.

Participants must not:Have used any investigational product within the 90 days prior to study product administration or plan to use any investigational products during the period of study participationHave consumed (by ingestion or topical application) any herbal or other traditional medication within 14 days of study product administrationHave a history of serious reactions to any prior vaccination or known hypersensitivity to any component of the MRV-MNP, MRV-SC, or PLA-MNP including polyethylene foam with acrylic adhesive, silicone-coated Kraft paper, stainless steel and severe allergic reactions to cow’s milkHave a history of anaphylactic shock or other life-threatening allergic reactionsHave any chronic, clinically significant pulmonary, cardiovascular, hepatobiliary, gastrointestinal, renal, neurological or haematological abnormality or illness that requires medical therapy, as determined by medical history, physical examination and laboratory assessmentHave a history of administration of any non-study vaccines within the 56 days before the administration of study products or planned vaccination during study participation, except for non-measles and rubella catch-up/national campaign administered through the Gambian Ministry of HealthHave a history of chronic administration (defined as more than 14 consecutive days) of immunosuppressant (> 0.5mg/kg/day of prednisolone or equivalent) or other immune modifying drugs within the 12 months prior to the administration of the study vaccine including the use of glucocorticoids. The use of inhaled/per nasal glucocorticoids will be permitted. The use of topical glucocorticoids within 12 months is not permitted (specific enquiry regarding the use of skin lightening creams should be made)Have a history of the administration of immunoglobulins and/or any blood products within the 12 months prior to administration of the study vaccine or anticipation of such administration during the study periodHave a history of known disturbance of coagulation or blood disorder that could cause anaemia or excess bleeding (e.g. sickle cell disorders, thalassemia and coagulation factor deficiencies)Have a history of keloid formationHave significant scars, tattoos, rashes or other dermatologic conditions in the area of the vaccination site which will interfere with the application of the MNP and assessment of local solicited AEHave HIV, hepatitis B or hepatitis C infection based on screening laboratory investigationsHave any medical or social condition that in the opinion of the study clinician may interfere with the study objectives, pose a risk to the participant or prevent the participant from completing the study follow-upBe an employee of or direct descendant (child or grandchild) of any person employed by the investigator or sponsorHave plans to travel outside the study area for an extended duration during the period of study participationThis is particularly critical in the first 42 days following study product administration during which any travel will be actively discouraged. At later timepoints, short trips within The Gambia can generally be accommodatedHave any screening laboratory test with a toxicity score of ≥ 2 or with a toxicity score of 1 which is nonetheless judged to be clinically significant by the trial clinician. If judged to be clinically indicated, each laboratory assessment may be repeated once during the screening period, with the most recent laboratory value being used for evaluation of exclusion criteria. However, abnormal laboratory investigations will not ‘routinely’ be repeated unless there is a clinical indication as to why the initial result was abnormal and it is considered likely that the abnormality will have resolvedHave any vital sign (heart rate, respiratory rate, non-invasive blood pressure [BP] [adult cohort only]) with a toxicity score of > 1. An abnormal vital sign may be repeated once during the screening period for a participant to remain eligible for randomization with the most recent set of vital signs being used to determine final eligibility§Have an axillary temperature of > 37.5°C and have had a documented fever at the same level in the 72 h preceding randomization and vaccination§Have a history of an illness with a fever and rash suggestive of measles in the preceding 2 months.Have any acute illness (severity grade > 2)§Have a positive rapid diagnostic test (RDT) (or blood film) for malaria. If a participant initially has a positive RDT and is then treated, a blood film will be undertaken if the RDT remains positive, to confirm treatment success given an RDT may remain positive even following successful treatment§Adult cohort only: have been vaccinated against measles or rubella in the preceding 4 yearsAdult cohort only: have a body mass index (BMI) of < 18.5kg/m^2^ (underweight) or > 35kg/m^2^ (severely obese)Adult cohort only: have a recent history (within the past year) or signs of alcohol or substance abuseAdult cohort only: have a history of major psychiatric disorderAdult cohort only: have a history of blood donation within three months of study enrolment or plans to donate blood during participation in the studyAdult female cohort only: be pregnant or breast-feedingToddler and infant cohort only: have been vertically exposed to HIV based on maternal history (mothers of potential participants will not be tested for HIV as part of screening)Toddler and infant cohorts only: have a weight for height *z*-score below −2SD (moderate malnutrition)Infant cohort only: have been vaccinated against measles or rubella§Participants with an acute illness, fever, other abnormal vital signs or a positive malaria RDT test may return once for a repeat screening visit within the 2-week screening period and still qualify for randomization if the acute illness has resolved. A minimum of 72 h following a documented fever (axillary temperature ≥ 37.5°C) must pass before a participant can be re-screened and vaccinated. In general, illnesses lasting more than the 2-week screening window will be considered to define a potential participant as a screen failure although a participant providing ongoing informed consent could be fully rescreened under such circumstances in the absence of any other reasons to define them as such.Specific exclusion criteria (vital signs, clinical examination, history of acute illness, blood test for malaria, urinary pregnancy test [adult female cohort only]) will be reassessed at the time of visit 1 and prior to confirming final eligibility and proceeding to randomization to ensure only those participants appropriate for vaccination on the day are included in the study.

All eligibility criteria will be assessed by a study clinician delegated by the principal investigator who will have overall responsibility for participant eligibility. The laboratory assessments undertaken as part of eligibility screening will be undertaken in the MRCG ISO15189-accredited CSD laboratories.

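### The fever exclusion and the note attached to it use different cut-offs (> 37.5°C and ≥ 37.5°C), and the criterion's *and*, taken literally, is looser than the note

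*Protocol article*

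**What the plan says.** The fever rule appears twice in the Exclusion criteria of the Protocol article.

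- The criterion, under the stem that participants must not meet it: "Have an axillary temperature of > 37.5°C and have had a documented fever at the same level in the 72 h preceding" randomization and vaccination. It carries a § mark.
- The § note, on deferral: "A minimum of 72 h following a documented fever (axillary temperature ≥ 37.5°C) must pass before a participant can be re-screened and vaccinated".
- The same note, on who may come back: "Participants with an acute illness, fever, other abnormal vital signs or a positive malaria RDT test may return once for a repeat screening visit". Fever is listed there as a reason in its own right.

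Two features of the list bear on how the criterion is read. It opens with "A prospective participant will not be eligible for enrolment if they meet any of the following exclusion criteria". Elsewhere it joins alternatives with *or*, for example "Have used any investigational product within the 90 days prior to study product administration or plan to use any investigational products".

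The neighbouring limits do not supply a temperature cut-off. The vital-sign criterion names heart rate, respiratory rate and, in adults, blood pressure. The acute-illness criterion is "Have any acute illness (severity grade > 2"), so it does not reach milder illness.

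**The concern.** An eligibility threshold should be stated once, or identically wherever it is repeated. Here the criterion and its own note use the same term, a documented fever, with two cut-offs. The criterion's wording can also be taken to need two fevers where the note needs one.

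What is at stake is a clear rule at the point of dosing and in the later check of eligibility. Study clinicians apply the criteria at screening and again at visit 1. Data management is to flag eligibility deviations (Data management {19}), and the blinded review is to consider breaches of the inclusion and exclusion criteria (section {20c}). A participant dosed at exactly 37.5°C complies with the criterion, yet can be classed as a deviation under the note. This is the first use of the MRV-MNP in humans, with cohorts down to 9 months of age, so the listed criterion should not be the looser of the two texts.

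**Working it through.** The plan gives no figure to reproduce here. The check sets the two texts side by side.

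**Inputs** (all from Exclusion criteria unless stated)

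- Criterion: temperature now > 37.5°C, *and* a documented fever at that same level in the preceding 72 h.
- Note: a documented fever is ≥ 37.5°C, and 72 h must then pass.
- Screening window: day −14 to day −1, that is 14 days (Participant timeline {13}, Table 1).
- Assumption: temperatures are recorded to 0.1°C. The article gives no resolution.

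**Step 1: the cut-off**

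| Reading | Criterion (> 37.5) | Note (≥ 37.5) | Agree? |
|---|---|---|---|
| 37.4°C | no | no | yes |
| 37.5°C | no | yes | no |
| 37.6°C | yes | yes | yes |

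At 0.1°C resolution the two cut-offs differ on exactly 1 recordable value.

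**Step 2: the connective**

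The criterion allows two readings. Reading A: a person is excluded only if both halves are true. Reading B: each half is forbidden separately. The last column applies the note's 72 h rule to anyone with a documented fever. The 38.5°C values are illustrative.

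| Temperature now | Documented in prior 72 h | Criterion, reading A | Criterion, reading B | Note |
|---|---|---|---|---|
| 38.5°C | none | not excluded | excluded | wait 72 h |
| below 37.5°C | 38.5°C, 24 h ago | not excluded | excluded | wait 72 h |
| 38.5°C | 38.5°C | excluded | excluded | wait 72 h |
| exactly 37.5°C | none | not excluded | not excluded | counts as fever |
| below 37.5°C | exactly 37.5°C | not excluded | not excluded | counts as fever |
| below 37.5°C | none | not excluded | not excluded | no wait |

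Reading A conflicts with the note in rows 1 and 2, and reading B removes that conflict. The difference in cut-off, rows 4 and 5, remains under both readings of *and*.

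**Step 3: does the proposed wording close the gap?**

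With *axillary temperature ≥ 37.5°C, or a documented fever ≥ 37.5°C in the preceding 72 h*, rows 1 to 5 are all excluded or deferred and row 6 is not. That matches the note in every row.

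**Step 4: does the deferral fit the schedule?**

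72 h = 3 days, and 14 − 3 = 11. A fever documented by day 11 of the window (study day −4) can be re-screened by day −1, using the one repeat visit that the note allows. A fever first found later in the window, or at visit 1, may not fit.

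**The case against.** Four points can be made on the other side.

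1. *The note may be only a return rule.* It says when someone may be re-screened and vaccinated, so it can be taken to govern only people already deferred. Someone at exactly 37.5°C who never met the criterion would then face no wait. This stands as a possible reading. A reader might infer that the two texts collide in practice at 37.5°C whatever the interpretation, and the document does not support that. What remains on this reading is one term with two cut-offs.

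2. *The connective is read too literally.* After *must not*, joining two conditions with *and* can naturally forbid each of them. The list also uses *and* loosely elsewhere: the hypersensitivity criterion ends with severe reactions to cow's milk joined to the patch materials by *and*, and no one would require all of those together. The note's separate listing of fever points the same way. This stands. The stricter sense is evidently meant, so the connective is a secondary wording fault that depends on the reading.

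3. *Other safeguards exist.* A study clinician may exclude anyone with a medical condition that poses a risk, and vital signs, examination and acute illness are reassessed at visit 1. A reader might infer that the protocol lets plainly febrile infants be dosed. These safeguards and the note make that implausible. They set no temperature cut-off, however, so they do not settle which symbol is right.

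4. *Little follows from it, and the change is not free.* Both are true. The consequence is small, and amendments go to two ethics committees and the Medicines Control Agency (section {25}) while recruitment is under way.

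**Conclusion.** The point holds as a minor inconsistency in current, operative text. The criterion and its note give different fever cut-offs, so exactly 37.5°C is a fever under one and does not meet the other. The criterion's *and* adds a second mismatch only if taken literally.

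The firm part amounts to one recordable value, assuming readings to 0.1°C. The number of participants cannot be estimated, because the article gives no baseline fever rate.

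A reader might go further and infer a threat to the randomized comparison. The document does not support that: eligibility is settled before randomization, so both arms face the same rule. No estimand, analysis or sample size changes.

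**What to change.** Reword the criterion to: axillary temperature ≥ 37.5°C at screening or at visit 1 before randomization, OR a documented fever (≥ 37.5°C) in the 72 h preceding randomization and vaccination. Keep ≥ 37.5°C in the § note, so that both places agree.

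The cost is one line of eligibility text in the next protocol version, with the usual ethics and regulatory approval. A few more people may be deferred for 72 h. Most such deferrals can use the existing single repeat visit. Fevers first found late in the 2-week window or at visit 1 may need full re-screening.
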